### Data analysis

Analyses will employ linear mixed-effects models (LMMs) to evaluate changes in VIA-Youth questionnaire and SDQ responses over time and between intervention and control groups, accounting for the nested structure of students within schools. A random intercept for each school will be included to adjust for intra-cluster correlation. Fixed effects will include intervention group, time, student sex, and grade, with interaction terms used to explore whether the intervention effect varies across these factors.

All statistical analyses will be performed using SPSS. The significance level will be set at α = 0.05, and results will be reported with 95% confidence intervals.

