## Methods

### Study design and study population

The Leadership, Empathy, Altruism, Personal Growth, & Social Responsibility (LEAPS) program will be a school-based intervention that will be implemented and evaluated using a cluster-randomized pre-post study design in the Gampaha district. Gampaha has been selected for its diversity and feasibility. The district offers a multiethnic student population from diverse socioeconomic backgrounds, enhancing the generalizability of the study. Additionally, the presence of the University of Kelaniya within Gampaha ensures proximity and accessibility for researchers, facilitating implementation. The district’s zonal education office has authorized the project and distribution of school invitations. Schools selected for participation possess the necessary IT infrastructure to host the intervention platform. The zonal education office will also obtain approvals from school principals and teachers, and invite students in grades 7–9 (aged 12–14) to participate, ensuring parental consent is obtained beforehand. To participate in the study, students must be able to use web applications and comprehend Sinhalese.

After consent is obtained, ten schools will be randomly assigned (using a computer-generated algorithm) to either receive the intervention or be placed on a waitlist. The intervention group will partake in weekly LEAPS sessions during their IT class periods over a 10-week span. The waitlist group will receive the program 3 months after the intervention group begins the study. Both groups will continue receiving their regular school curriculum throughout the study. Assessments will be conducted at three time points: baseline (t_1_), immediately post-intervention (t_2_, 2.5 months), and 6-months post-intervention (t_3_) (see Fig. 1).

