### Power and sample size determination

Twenty schools in the Gampaha district of Sri Lanka have the necessary digital infrastructure to support the intervention. The study team will randomly assign ten schools to the intervention arm and ten to the control arm. An a priori power analysis for a two-arm cluster randomized design has been conducted [34–36] to confirm the feasibility of using 20 clusters to detect a small effect size (Cohen’s *d* = 0.25; 37) with a desired power of 90% and a significance level of 0.05.

Under individual randomization, we used G*Power 3.1 (two-sample t test: difference between two independent means, two-tailed) with *d* = 0.25, α = 0.05, and power = 0.90, yielding a required sample size of ~ 337 participants per arm. To adjust for clustering, we assumed an intraclass correlation coefficient (ICC) of 0.01 based on estimates from previous school-based interventions [38]. Assuming an average of 150 students per school agree to participate, the design effect was calculated as:$$\begin{aligned} \mathrm{Design}\;\mathrm{effect}\;&=\;1\;+\;\lbrack(\mathrm m-1)\;\times\;\mathrm{ICC}\rbrack\;\\&=\;1\;+\;\lbrack(150-1)\;\times\;0.01\rbrack\;\\&=\;2.49 \end{aligned}$$

After multiplying the sample size by this design effect, we obtained the adjusted sample size of 839 per arm. To account for an anticipated 30% attrition rate, the study team will recruit approximately 1,200 students per arm (2,400 total). While simulation-based power analyses are ideal for clustered and repeated data, they require parameter estimates and resources that are currently unavailable to the study team. In this context, applying the design effect to an individual-level calculation is a transparent and widely accepted approach in cluster-randomized trials [34–36].

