### Ethical considerations

The study has been approved by the ethics board at the University of Kelaniya and registered with the Sri Lanka Trials Registry (No: *SLCTR/2020/016*). The authors obtained permission from the Western Province Department of Education, relevant Zonal Education Offices for the District of Gampaha, and from principals of the selected schools to recruit teachers and students. To obtain parental consent, researchers and teachers will provide students with (1) an information sheet, (2) a parental consent form, and (3) an opt-out form for parents who do not wish for their child to participate. All students will be informed that participation is voluntary, that LEAPS is not part of their regular syllabus, and that they can withdraw their consent and leave the study at any time.

Participants will be assigned a unique, anonymous code that will be used on all their data forms. Electronic data will be stored on password-protected computers and hard copies will be stored in locked storage facilities at the University of Kelaniya. Access to these computers and facilities will be restricted to members of the research team. Consent forms will be stored separately to prevent linking participant names with their codes and associated data.

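### The stated mixed model has a school random intercept but no student-level or school-by-time term, so fitted as written it generally gives the wrong standard error for change between arms

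*Protocol article*

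**What the plan says.** The Data analysis section sets the target of the models as to "evaluate changes in VIA-Youth questionnaire and SDQ responses over time and between intervention and control groups". It describes the dependence to be handled as "accounting for the nested structure of students within schools" and names one random effect: "A random intercept for each school will be included to adjust for intra-cluster correlation". The rest of the specification is fixed effects: "Fixed effects will include intervention group, time, student sex, and grade, with interaction terms used to explore whether the intervention effect varies across these factors".

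The data have a further level. Under Study design and study population, "Assessments will be conducted at three time points": baseline (t1), end of intervention at 2.5 months (t2), and 6 months post-intervention (t3). The LEAPS evaluation section gives the scales to the students on each occasion. Ethical considerations shows that records can be linked within student: "Participants will be assigned a unique, anonymous code that will be used on all their data forms".

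No student random effect, within-student covariance or school-by-time effect is named anywhere. The Power and sample size determination section calls the data clustered and repeated, but only when explaining why power was not simulated.

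**The concern.** There are three levels here: occasions within students within schools. The stated structure covers one of the two groupings, and covers it in a form that does not serve the contrast of interest.

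In a pre-post design the treatment effect is the between-arm difference in change, that is, the group-by-time contrast. Two sources of variation matter for its SE and neither is in the stated model:

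- **Stable differences between students.** They cancel from a student's change score. A model without a student term leaves them in the residual, so the SE is too large and the baseline measurement is largely wasted.
- **School-by-time variation**, meaning schools drifting differently for reasons unrelated to the programme. This is the cluster-level error for a change contrast. A constant school intercept subtracts out of t2 minus t1 and does not represent it, so the SE is too small and rests on thousands of residual degrees of freedom when there are only 20 schools.

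The two errors pull in opposite directions. At stake are the nominal 0.05 level and the 95% confidence intervals for the treatment effect on the primary measure, the VIA-Youth.

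**Working it through.** **Inputs from the article.** Ten schools per arm: "The study team will randomly assign ten schools to the intervention arm and ten to the control arm". (Study design and study population speaks of ten schools being randomised; the 20 of the power and randomisation sections is used here.) ICC 0.01. Target effect d = 0.25. Design effect 2.49. Three occasions.

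**The article's own figures reproduce.** It states "α = 0.05, and power = 0.90, yielding a required sample size of ~ 337 participants per arm". The normal formula 2(1.960 + 1.282)²/0.25² gives 337. Then 337 × 2.49 = 839 per arm, and 840/0.7 = 1,200 recruited per arm. That is about 839/10 ≈ 84 analysed, or 120 recruited, per school. The sample size is not in dispute.

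**Assumptions.** The article gives neither the within-student correlation ρ nor the cluster autocorrelation c (the share of school variance that is constant over time). I take ρ = 0.6 and c = 1, 0.8 or 0.5. Total variance is 1 and the data are balanced.

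**Variance components.** School-by-time: ICC(1 − c). Student: (1 − ICC)ρ. Residual: (1 − ICC)(1 − ρ).

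**Formulas**, with m students per school, 10 schools per arm and N = 10m, for the t2 minus t1 difference between arms:

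- True variance = 4 × residual/N + 4 × school-by-time/10.
- Variance reported by the school-intercept model ≈ 4 × (student + residual + school-by-time)/N.
- With r = reported SE/true SE, type I error ≈ 2Φ(−1.96r).

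**Worked case**, m = 84, ICC 0.01, c = 1: the true variance is 4 × 0.396/840 = 0.00189, so the SE is 0.043. The reported variance is 4 × 0.99/840 = 0.00471, so the SE is 0.069. Hence r = 1.58 and type I error is about 0.2%.

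| ICC | c | True SE | Reported SE | r | Type I error |
|---|---|---|---|---|---|
| 0.01 | 1 | 0.043 | 0.069 | 1.58 | 0.2% |
| 0.01 | 0.8 | 0.052 | 0.069 | 1.33 | 0.9% |
| 0.01 | 0.5 | 0.062 | 0.069 | 1.10 | 3.0% |
| 0.05 | 0.8 | 0.076 | 0.068 | 0.89 | 8.2% |
| 0.05 | 0.5 | 0.109 | 0.068 | 0.63 | 21.9% |

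**Where the errors cancel.** Setting the two variances equal gives student variance = (m − 1) × school-by-time variance. With m = 84 and ICC 0.01, the school-by-time variance would have to be 0.594/83 = 0.0072, or 72% of the school variance. At ICC 0.05 it is 0.570/83 = 0.0069, or 14%.

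**Other settings.** With 120 per school and ρ = 0.5, r at ICC 0.01 is 1.41, 1.16 and 0.95 for c = 1, 0.8 and 0.5 (type I error 0.6%, 2.3% and 6.2%). At ICC 0.05 with c = 0.8 and 0.5, r is 0.76 and 0.53 (type I error about 14% and 30%). Simulation with 1,000 trials per setting agreed with the closed-form ratios to within about 0.06.

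**The partial repair.** Adding only a student random intercept, with 120 per school, ρ = 0.5 and c = 0.8, gave simulated r = 0.85 and type I error 10% at ICC 0.01, and r = 0.53 and 29% at ICC 0.05.

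**The case against.** The strongest reply is that the article names a school intercept for one purpose and does not say that this is the whole covariance structure. In SPSS MIXED the within-subject covariance is specified separately from the random effects, and an unseen analysis plan may hold it. Residual covariance and the degrees-of-freedom method are commonly left to such a plan. This stands in part. A reader might infer that the authors have ruled out a student-level term or declared residuals independent; the text does neither. But it is not merely silent: it states a target (change), a nesting and a random effect with its purpose. For a change contrast, that random effect does not achieve that purpose. Degrees of freedom alone would be no finding.

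The second reply concerns size, and it also stands. A reader might infer that the planned test yields too many false positives. The article's own ICC does not support that: at 0.01 the type I error stays below 5% in every row of the table, and the highest value in the other settings shown is 6.2%. The clear inflation needs a larger ICC with appreciable school-by-time variance. Nor is the SE wrong in every case, since the two errors can cancel.

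Third, the conservative error does not by itself sink the trial. In the worked case the model rejects when the estimate exceeds 1.96 × 0.069 = 0.135. A true difference of 0.25 is then detected with probability about Φ((0.25 − 0.135)/0.043), above 99%. The loss falls on interval width and on effects smaller than the target.

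**Conclusion.** The point holds for the group-by-time contrast. As written, the random-effects structure does not match a cohort measured three times, and the reported SE is right only if both omitted components are zero or happen to cancel.

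At ICC 0.01 the likelier result is an SE that is too large, with lost precision and power: up to 1.58 times the true value in the table, a 95% half-width of about 0.135 where 0.085 would do. At ICC 0.05 with c between 0.8 and 0.5 the SE is too small, with type I error of about 8% to 22%. These sizes rest on the assumed ρ and c, balanced data and 84 students per school.

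The time-averaged difference between arms is largely protected by the school intercept in balanced data, so the point does not extend to it. The sample size figures are also unaffected.

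**What to change.** Restate the model in the Data analysis section, before data are seen, with:

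- a random intercept for school;
- a random school-by-time effect;
- a student-level term: either a student random intercept nested in school, or an unstructured residual covariance over the three occasions within student;
- Satterthwaite or Kenward-Roger degrees of freedom, because there are only 20 schools.

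A student intercept should not be added on its own. As shown above, it removes the conservative error and exposes the anticonservative one.

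A valid alternative is an ANCOVA at each of t2 and t3, with the student's own baseline score as covariate and a school random intercept. It is not equivalent: it estimates adjusted differences at single occasions and treats missing data differently, which matters with 30% attrition expected. Run at t2 only, it would leave out the planned t3 assessment.

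The cost is a few lines of SPSS MIXED syntax and a sentence or two of text, with no extra data. With 20 schools the school-level variance components may be imprecisely estimated.

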### Randomization

To assign the 20 schools to the intervention and control arms, allocation will be generated using a computer-based random sequence prepared by an independent statistician. Randomization will be 1:1 and stratified by school size (based on number of eligible students), with allocation concealed until assignment.

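### Schools are randomised within size strata, but the fixed effects named for the model omit the stratum; if school size is prognostic, a between-arm level comparison is less precise than it could be

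*Protocol article*

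**What the plan says.** All references are to the protocol article.

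- **Randomization:** "Randomization will be 1:1 and stratified by school size (based on number of eligible students), with allocation concealed until assignment". The number of strata and the cut-points are not given.
- **Data analysis:** the linear mixed models for VIA-Youth and SDQ are described by "Fixed effects will include intervention group, time, student sex, and grade", "with interaction terms used to explore whether the intervention effect varies across these factors". The only random effect named is for school: "A random intercept for each school will be included to adjust for intra-cluster correlation". Neither school size nor the stratum appears.
- **Power and sample size determination:** "The study team will randomly assign ten schools to the intervention arm and ten to the control arm". The calculation is a two-sample comparison of means inflated by a design effect, for which "we assumed an intraclass correlation coefficient (ICC) of 0.01".

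**The concern.** Stratified allocation makes the arms alike on the stratification factor, so differences between strata no longer contribute to the true sampling variance of the arm comparison. A model without the stratum does not know this. It leaves the between-stratum differences in the estimated school-level variance, and the reported standard error can then exceed the true one. The interval over-covers and the test rejects less often than its nominal 5%.

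The named covariates include two that played no part in allocation (sex and grade) and leave out the one that did. With 20 schools, between-school information is scarce, so precision already secured by the design should not be given away in the analysis. Any loss depends on two things that the article does not settle: whether school size is related to the outcomes, and whether the treatment effect is a comparison of levels or of changes.

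**Working it through.** **1. The plan's own figures.** With d = 0.25, two-sided alpha 0.05 and power 0.90, n = 2 × (1.960 + 1.282)² / 0.25² ≈ 337 per arm. The design effect is 1 + 149 × 0.01 = 2.49, and 337 × 2.49 = 839. Allowing for 30% attrition, 839 / 0.70 = 1,199, or about 1,200. All three figures reproduce, and this point changes none of them.

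**2. Inputs for the check.**
- From the article: 10 schools per arm, ICC 0.01, about 1,200 recruited per arm, 30% attrition. Analysed students per school: m = 1,200 / 10 × 0.70 = 84.
- Assumed, because the article does not give them: R2, the share of between-school variance explained by the size stratum (0 to 0.5), and the number of strata (2, with 4 as an alternative). The total SD is set to 1.

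**3. Between-arm level comparison.** The school share of the variance of a school mean is 0.01 / (0.01 + 0.99/84) = 0.01 / 0.02179 = 0.459. The variance of the arm difference is (2/10) × [ICC × (1 - R2) + (1 - ICC)/m].

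With the stratum omitted, the model estimates this with R2 = 0: SE = √(0.2 × 0.02179) = 0.0660. With t on 18 df (2.101), the half-width is 0.1387.

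With two strata included, t is on 17 df (2.110):

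| R2 (assumed) | SE | 95% half-width | Change in CI width |
|---|---|---|---|
| 0 | 0.0660 | 0.1393 | +0.4% |
| 0.1 | 0.0645 | 0.1360 | -2% |
| 0.3 | 0.0613 | 0.1293 | -7% |
| 0.5 | 0.0579 | 0.1222 | -12% |

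On the variance scale, R2 = 0.3 is a reduction of 0.3 × 0.459 = 13.8% and R2 = 0.5 one of 22.9%. CI width is the fairer scale because it takes the square root and charges the lost degree of freedom. With four strata (15 df) and R2 = 0, the interval is 1.5% wider.

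Sensitivity: with the article's 150 students per school, m = 150 × 0.70 = 105, and the changes at R2 = 0.3 and 0.5 are about -8% and -13.5%. At an assumed ICC of 0.05 with m = 84, the four changes are about +0.4%, -4%, -13% and -23%.

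**4. Size of the test.** Stratified allocation of 20 schools was simulated (two strata, ICC 0.01, 8,000 runs per setting; Monte Carlo error about √(0.05 × 0.95 / 8,000) = 0.0024). With the stratum omitted, the type I error of the nominal 5% test was 0.048, 0.043, 0.033 and 0.023 at R2 = 0, 0.1, 0.3 and 0.5. With it included, it was 0.046 to 0.049. Omission never inflated the error, and it made the test conservative only when size was prognostic.

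**5. Group-by-time comparison.** With a school random intercept and equal numbers at two visits, a time-constant school effect cancels from each school's change, and the stratum main effect cancels with it. The SE is √[(2/10) × 2 × (1 - ICC)/m], which contains no R2. At ICC 0.05 this is √(0.2 × 2 × 0.95/84) = 0.0673. Fitting the mixed model to 60 simulated data sets (ICC 0.05, R2 0.5) gave 0.0672 without the stratum and 0.0672 with it.

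**The case against.** The strongest reply is that the section sets out to evaluate changes over time between groups. A group-by-time effect is therefore a natural reading, and for that contrast a stratum main effect buys no precision. This stands for that contrast. It does not dispose of the point, because the article never names the contrast that carries the treatment effect. It describes interactions as exploratory, "with interaction terms used to explore whether the intervention effect varies across these factors", and the sample size rests on a comparison of two independent means, which is a level comparison. Even for change, a stratum whose effect differs over time could still matter.

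Second, nothing in the article shows that school size predicts VIA-Youth or SDQ scores. Size is defined by the number of eligible students, so the aim may simply have been to balance student numbers between arms. This also stands: R2 may be zero, and the term would then cost slightly more than it returns.

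Third, the list of fixed effects may not be exhaustive, and an analysis plan that is not shown could add the stratum. That is possible. However, the article does name its covariates, so this is a stated choice that departs from the design and not just a detail left out.

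**Conclusion.** The mismatch is real: allocation is stratified by school size, and the named fixed effects leave that factor out.

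A reader might infer that the standard error is certainly too wide. The document does not support that. The loss exists only if school size is prognostic, on which the article is silent, and only for a between-arm level comparison. Under ICC 0.01, 84 analysed students per school and two strata, including the stratum would change the CI width by between +0.4% and -12% over an assumed R2 of 0 to 0.5.

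A reader might also infer that the analysis is invalid. It is not: the estimate is unbiased with respect to this factor, type I error is not inflated, and any error is on the conservative side. The point is minor. It is worth raising because the possible gain is larger than the cost of including the term.

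**What to change.** In Data analysis, add the school-size stratum, coded as it is used in the randomisation, to the fixed effects of the VIA-Youth and SDQ models. If the treatment effect is estimated as group-by-time, add stratum-by-time as well, because the main effect alone does nothing for that contrast. If the stratum is to be left out, say why.

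The cost is (strata - 1) of the 18 between-school degrees of freedom: 1 with two strata and 3 with four. If size proves unrelated to the outcome, the CI is 0.4% or 1.5% wider respectively. No new data are needed, since stratum membership is known at allocation, and the sample size does not change. Fixing the term now also avoids a decision on adjustment after the data have been seen.

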### Power and sample size determination

Twenty schools in the Gampaha district of Sri Lanka have the necessary digital infrastructure to support the intervention. The study team will randomly assign ten schools to the intervention arm and ten to the control arm. An a priori power analysis for a two-arm cluster randomized design has been conducted [34–36] to confirm the feasibility of using 20 clusters to detect a small effect size (Cohen’s *d* = 0.25; 37) with a desired power of 90% and a significance level of 0.05.

Under individual randomization, we used G*Power 3.1 (two-sample t test: difference between two independent means, two-tailed) with *d* = 0.25, α = 0.05, and power = 0.90, yielding a required sample size of ~ 337 participants per arm. To adjust for clustering, we assumed an intraclass correlation coefficient (ICC) of 0.01 based on estimates from previous school-based interventions [38]. Assuming an average of 150 students per school agree to participate, the design effect was calculated as:$$\begin{aligned} \mathrm{Design}\;\mathrm{effect}\;&=\;1\;+\;\lbrack(\mathrm m-1)\;\times\;\mathrm{ICC}\rbrack\;\\&=\;1\;+\;\lbrack(150-1)\;\times\;0.01\rbrack\;\\&=\;2.49 \end{aligned}$$

After multiplying the sample size by this design effect, we obtained the adjusted sample size of 839 per arm. To account for an anticipated 30% attrition rate, the study team will recruit approximately 1,200 students per arm (2,400 total). While simulation-based power analyses are ideal for clustered and repeated data, they require parameter estimates and resources that are currently unavailable to the study team. In this context, applying the design effect to an individual-level calculation is a transparent and widely accepted approach in cluster-randomized trials [34–36].

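### The design effect is built on 150 students per school, which does not fit ten schools and about 1,200 recruits per arm, and the number of schools enters no step; at the stated ICC the error is conservative

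*Protocol article*

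**What the plan says.** The section Power and sample size determination assigns ten schools to each arm. It gives the purpose of the calculation as "to confirm the feasibility of using 20 clusters" for d = 0.25, with a "desired power of 90% and a significance level of 0.05". The steps are:

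- An individual-level calculation ("two-sample t test: difference between two independent means, two-tailed"), "yielding a required sample size of ~ 337 participants per arm".
- A design effect with ICC 0.01: "Assuming an average of 150 students per school agree to participate, the design effect was calculated as" 1 + (150 − 1) × 0.01 = 2.49.
- An adjusted sample size of 839 per arm.
- An allowance for 30% attrition, after which "the study team will recruit approximately 1,200 students per arm (2,400 total".

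The Randomization section also refers to 20 schools, stratified by size. The section Study design and study population instead describes ten schools being randomised between intervention and waitlist.

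**The concern.** Ten schools per arm, 150 participating students per school and 1,200 recruits per arm cannot all hold. Any two of them fix the third at a different value from the one printed.

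The cluster size matters because it drives the design effect, and through it the 839 and the 1,200. The figure of 839 is the number needed before the attrition allowance is added, so the matching cluster size is the number analysed per school, not the number who agree to take part.

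The number of schools matters because it limits what extra students can achieve. With k schools per arm, the effective sample size per arm cannot exceed k/ICC. A calculation that never uses k gives the same answer for 6 schools as for 60, so it cannot support a statement about 20. At stake are one unambiguous enrolment target and a power statement that describes the trial as laid out.

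**Working it through.** **Inputs from the protocol article:** d = 0.25 (SD 1), two-sided α = 0.05, target power 0.90, ICC 0.01, m = 150 in the design effect, attrition 30%, 10 schools per arm, about 1,200 recruited per arm.

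**1. The printed chain reproduces.** The normal approximation gives 337 per arm (338 by the noncentral t). The design effect is DE = 1 + 149 × 0.01 = 2.49. Then 337 × 2.49 = 839.1, and 839 / 0.7 = 1,199, or about 1,200. No step contains an arithmetic slip.

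**2. It does not fit the layout.**
- 10 × 150 = 1,500 per arm (3,000 in total), not 1,200 (2,400).
- 1,200 / 10 = 120 recruited per school; 120 × 0.7 = 84 analysed per school.
- 1,200 / 150 = 8 schools per arm, not 10.

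The 120 and 84 are derived here and are not printed in the article.

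**3. The protocol's own formula with the analysed cluster size.** With m = 84, DE = 1 + 83 × 0.01 = 1.83. Then 337 × 1.83 = 616.7, so about 617 analysed per arm, and 616.7 / 0.7 = 881 recruited. Even with m = 120, DE = 2.19 and the requirement is 738 analysed per arm.

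**4. Power for ten schools per arm.** The noncentrality is d / √(2 × DE / n) with n = 10m, referred to t with 2 × 10 − 2 = 18 df.
- m = 84: 0.25 / √(2 × 1.83 / 840) = 3.79, power 94.7% (96.6% by the normal approximation).
- m = 105 (150 less 30%): DE = 2.04, 0.25 / √(2 × 2.04 / 1,050) = 4.01, power 96.6% (98.0% by the normal approximation).

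**5. Dependence on the ICC.** Values above 0.01 are assumed for sensitivity and do not come from the documents. Power with t on 18 df:

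| ICC | 84 per school | 105 per school |
|---|---|---|
| 0.01 (stated) | 94.7% | 96.6% |
| 0.02 (assumed) | 84% | 87% |
| 0.03 (assumed) | 74% | 76% |

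Power reaches 90% at an ICC of 0.0148 with 84 per school and 0.0172 with 105. At ICC 0.03 the effective sample size per arm is capped at 10 / 0.03 = 333, below the 337 required, whatever the school size. The printed formula cannot show this limit.

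**6. Unequal school sizes.** With an assumed size CV of 0.5, DE = 1 + ((1 + 0.25) × 84 − 1) × 0.01 = 2.04. Power for 840 analysed per arm at ICC 0.01 is then 92.4%.

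**7. If only ten schools were randomised.** Five per arm with 168 analysed each (840 per arm) gives DE = 1 + 167 × 0.01 = 2.67. Power is about 78% with t on 8 df, or 88% by the normal approximation.

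**The case against.** The strongest defence is that the mismatch does no harm at the stated ICC. A cluster size that is too large inflates the design effect, so the plan recruits more than it needs. The 90% is worded as a desired value, and it is met. This stands, and it sets the direction of the finding. A reader might infer that the trial is underpowered. The documents do not support that, since with 20 schools at ICC 0.01 power is about 95%.

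A second defence reads 150 as expected supply and 1,200 as the requirement, so that 10 × 150 = 1,500 covers 1,200 and the claim of feasibility has meaning. That reading is possible, but the article never makes the comparison. It also leaves the design effect on a cluster size that is neither the recruited nor the analysed one.

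Third, applying a design effect to an individual-level sample size is an accepted method, and the article says openly that it did so without simulation. That is fair. Moving from the normal approximation to 18 df costs less than two points (96.6% to 94.7%). The method still needs the trial's own cluster size and a check against the fixed number of schools, and neither requires simulation.

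Fourth, a reader might conclude that the ICC is too low and that true power is 74% or less. Nothing in the documents shows 0.01 to be wrong, and the higher ICCs and the size CV are assumptions. The planned mixed model also includes baseline and can use students with incomplete follow-up. The 84 per school and the single-comparison power are therefore approximations to it.

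**Conclusion.** The calculation is wrong as written, in a way that is conservative at the protocol's own ICC. The cluster size of 150 does not fit ten schools and 1,200 recruits per arm, and the number of schools is never used, so the calculation does not confirm what it says it confirms. For the layout described, the protocol's own formula needs about 617 analysed (881 recruited) per arm, against the stated 839 and about 1,200. Power is about 95% against the 90% target.

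This rests on 20 schools, equal school sizes, 30% attrition spread evenly, ICC 0.01 and a single post-intervention comparison. The margin is finite: at 84 per school, 90% power holds only up to an ICC of about 0.015. If ten schools in total were meant, the figure of 95% no longer applies.

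**What to change.** 1. Reconcile the number of schools: Study design and study population has ten randomised, while Power and sample size determination and Randomization have 20.
2. Choose one enrolment figure: 120 per school (2,400 in total) or 150 per school (3,000 in total).
3. Restate the calculation with 10 schools per arm, the analysed cluster size (84 or 105) and 18 df. At ICC 0.01 this gives power of about 95% or 97%.
4. State the ICC up to which 90% power holds (about 0.015 at 84 per school, about 0.017 at 105). Label any higher ICC or school-size CV as an assumed sensitivity value.

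The cost is one rewritten paragraph and one corrected school count. No extra recruitment is needed provided 20 schools are randomised.
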